### Sample size

The number of subjects required was calculated based on the data from Rose et al. [25] which showed a relative decrease in the PSS-10 score of 15% in the control group and 30% in the experimental group. Mean score values with a standard deviation (< 5) were reported. Given that the healthcare professionals recruited in our study will be under greater stressors than Rose et al.’s [25] study sample, which consisted of college students, the expected values of PSS-10 at baseline are 23 ± 5 with a decrease to 19.6 ± 5 in the control group and 16 ± 5 in the experimental group. Simulations using a mixed linear regression model showed that 46 subjects per group, i.e., 92 in total, would be needed to highlight a difference between groups with a power of more than 90% and an alpha risk set at 5%. Considering an estimation of 10% of exclusions (initial PSS-10 < 16) and 20% of drop-outs, the number of subjects in the study was increased to 120 subjects in total (Fig. 1).

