### Outcomes

#### Primary outcomes

The decrease of the Perceived Stress Scale – 10 items version (PSS-10) [30] score at 8 weeks will be our primary outcome. The 10 items of the PSS range from 0 (never) to 4 (very often); higher scores are indicative of higher perceived stress. The PSS-10 is validated in French [32], and its ease of use and psychometric properties have been widely studied in professional contexts [33]. The expected PSS-10 values are 23 ± 5 initially with a decrease to 19.6 (control group) and 16 (experimental group).

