### Statistical analyses

A descriptive analysis will be performed on the entire population and in each group (experimental and control). Categorical variables will be described, giving the numbers and frequency of each modality. Quantitative variables will be described using the usual positional and dispersion parameters. The data analyst will be blinded as he will not participate to data collection.

We will carry out the statistical analysis of the main judgment criterion using a mixed model, including a “group” effect (experimental or control), a time effect (J0 and S8), an interaction between the “group” and the “time,” and a “subjects” effect and a “center” effect. The “subject” and “center” effects will be random effects. The statistical test of interest will focus on the interaction term between group and time, which will assess whether the decrease in the PSS-10 score is greater in the experimental group than in the control group. In a second step, if this test is significant, we will estimate the decrease difference between the groups.

As of the analyses of secondary endpoints, we will assess the efficacy of online CBT on the prevention of PTSD, insomnia, and depression at 3 and 6 months using mixed regression models. In the case of restricted scores with values close to the extremes, we may use beta regression models after transformation of the variable of interest on a scale of ]0;1[. Regarding the predictive factors of the efficacy of online CBT, we will also use the aforementioned models, incorporating an interaction between group, time, and each potential predictive factor to test whether the improvement of scores in the CBT group relies on another factor. Also, we will carry out the identification of potential mediating factors explaining the effect of CBT on professional stress using Bayesian networks that allow learning the structure of a system from the data while integrating hypotheses about the structure. Mediation formulae will be used to assess total, direct and indirect effects. Finally, we will perform a descriptive analysis of the indicators of acceptability and satisfaction.

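### The primary between-group difference is to be estimated only if the group-by-time test is significant, so a null trial would report no model-based effect estimate or interval

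*Protocol article*

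**What the plan says.** The primary outcome (Primary outcomes) is a change: "The decrease of the Perceived Stress Scale – 10 items version (PSS-10) [30] score at 8 weeks will be our primary outcome". Under Statistical analyses it is modelled with a mixed model containing group, time (J0 and S8), their interaction, and random subject and centre effects. "The statistical test of interest will focus on the interaction term between group and time". The next step is conditional: "In a second step, if this test is significant, we will estimate the decrease difference between the groups".

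The same section also plans, without condition, a description of all variables overall and by group, using measures of position and dispersion. The document nowhere mentions a confidence interval. It sets no significance condition on estimation for the secondary endpoints.

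**The concern.** The sentence treats the size of the effect as something to look at only after a positive test. A non-significant result would then be published without the planned contrast and its precision. Two quite different null results would look the same: one whose interval excludes the difference the trial was designed to find, and one whose interval still contains it.

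The comparator is active and both arms have the hotline, so a true difference below the planned one is plausible. A null result is therefore a realistic outcome. A later synthesis would also receive the planned estimate only when it was large enough to be significant.

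This is an explicit rule, not a detail left to the analysis plan. An analysis plan that follows it inherits the problem, and one that always reports the estimate contradicts it.

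**Working it through.** **1. The estimate is not a second step.** Write the fixed part of the model as β0 + β1·group + β2·time + β3·group·time, with time 0 at J0 and 1 at S8.
- Decrease in the control group: −β2. Decrease in the experimental group: −(β2 + β3).
- Difference in decrease: −β3.

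The tested coefficient is, apart from its sign, the quantity the plan proposes to estimate later. The difference in week-8 scores is another contrast, β1 + β3. It equals β3 only if the modelled baselines are equal.

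**2. Inputs.**
- From Sample size: "a decrease to 19.6 ± 5 in the control group and 16 ± 5 in the experimental group", from a baseline of 23. The difference in decrease is (23 − 16) − (23 − 19.6) = 7 − 3.4 = 3.6.
- Also from Sample size: "46 subjects per group, i.e., 92 in total, would be needed", for power above 90% at 5% alpha.
- 120 recruited, with 10% exclusions and 20% drop-outs: 120 × 0.9 × 0.8 = 86.4, or about 43 per arm.
- Assumed, because not given: two-sided alpha, and a baseline to week 8 correlation ρ of 0.5. SD of change = 5·√(2(1 − ρ)) = 5 at ρ = 0.5.

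**3. The plan's own figure.** With 46 per arm, SE = 5·√(2/46) = 1.043. Power = Φ(3.6/1.043 − 1.96) = Φ(1.49) = 93.2%, in line with the stated power above 90%. A simulation of change scores gave 92.6%.

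**4. What the rule hides.** The smallest reportable estimate is the critical value × SE, which is also the 95% CI half-width. The chance that no estimate is reported is 1 − Φ(δ/SE − critical value), where δ is the true difference; the opposite tail is negligible here. The critical value is 1.96, except in the 43-per-arm row, which uses the t value 1.988.

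| Per arm | ρ | SE | Smallest reportable estimate | No estimate, δ = 3.6 | No estimate, δ = 1.8 |
|---|---|---|---|---|---|
| 46 | 0.5 | 1.04 | 2.04 | 6.8% | 59% |
| 43 | 0.5 | 1.08 | 2.14 | 8.8% | 62.5% |
| 46 | 0.7 | 0.81 | 1.58 | 0.6% | 39% |
| 46 | 0.3 | 1.23 | 2.42 | 17% | 69% |
| 46 | 0 | 1.47 | 2.89 | 31.5% | 77% |

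**5. What is lost after a null result.** Take 46 per arm and ρ = 0.5. An estimate of 0 has interval −2.04 to 2.04, which excludes the planned 3.6. An estimate of 1.9 has interval 1.9 ± 2.04, that is −0.14 to 3.94, which includes it. Neither is significant. Under the rule neither would be reported, although the first argues against the planned benefit and the second leaves it open.

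**The case against.** **Inflation.** A reader might infer that the sentence makes a positive result too large. The document does not support that. In a significant trial the coefficient is the same number under either wording, and its upward bias on average comes from significance and power. With 46 per arm and ρ = 0.5, the mean estimate given significance is 3.75 for a true 3.6 (+4%) and 2.79 for a true 1.8 (+55%). Both figures would remain after the sentence is changed. What the rule adds is that the smaller estimates never enter the record.

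**Nothing at all after a null result.** This is also too strong. The unconditional description by group would let a reader form a crude, unadjusted difference. The mediation analysis is said to assess total effects with no such condition, but it is not presented as the primary contrast. What is missing is the planned model-based estimate, with its centre effect and multiple imputation, and its interval.

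**Secondary outcomes.** One might extend the criticism to them, but the conditional wording concerns only the primary criterion.

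**Seriousness.** The rule leaves type I error, power, randomisation, data collection and the validity of the primary test untouched, and it can be put right from a model already fitted. That stands, and it makes this a reporting flaw of limited weight. The rule is still wrong as stated and concerns the main result.

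**Conclusion.** The point holds in limited form: the plan makes the primary effect estimate conditional on a significant test, and nothing else in the document supplies a model-based estimate and interval after a null result. Under the central assumptions (43 to 46 per arm, ρ = 0.5, two-sided 5% alpha), estimates smaller than about 2 points would not be reported. The trial would give no estimate with probability about 7 to 9% at the planned difference and about 59 to 62% at half of it. For ρ from 0.7 down to 0 with 46 per arm, the threshold runs from about 1.6 to 2.9 points. The existence of the flaw depends on none of these assumptions; only its size does.

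**What to change.** Under Statistical analyses, replace the conditional sentence with:

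*The difference between groups in the decrease in PSS-10 from J0 to S8 (the group-by-time interaction coefficient) will be reported with its 95% confidence interval whatever the result of the test.*

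The wording should name the difference in decrease and not the difference in week-8 scores. The latter is not the tested contrast, and its interval could disagree with the primary test.

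The cost is one sentence. The number of participants, alpha, power and the primary test stay as they are. No change is needed for the secondary outcomes.

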## Discussion

To the best of our knowledge, this will be the first randomized controlled trial comparing the efficacy and the acceptability of a brief online CBT program specifically developed for healthcare workers and of an active control group (i.e., bibliotherapy). Given the potential short- and long-term consequences of the COVID-19 pandemic on healthcare workers’ mental health, at an individual level, but also on healthcare systems, on a systemic level [11, 12, 17], our findings can significantly impact clinical practice and management of the ongoing, and probably long-lasting, health crisis [21].

Indeed, if our 7-session online CBT program produces a significant decrease on immediate perceived stress levels and improves the prevention of severe psychiatric disorders, such as PTSD and depression, it could become an empirically assessed viable option specifically suited to the needs of healthcare workers facing the COVID-19 pandemic and might be easily adapted to other sanitary crises. Indeed, in terms of format and content, this brief online CBT format has many advantages in the current context: first, similar programs have proved to improve resilience in highly stressful situations and prevent the emergence of psychological disorders [25]; second, it circumvents some of the pitfalls associated with face-to-face interventions (e.g., fear of contamination, and social distancing measures) and provides the flexibility required in order to facilitate its accessibility to a great number of healthcare workers [21]. In addition, we have chosen a step-by-step guided format rather than a free access to the program sessions in a random order. This format mimics the outline of standard face-to-face CBT possibly enhancing the effectiveness of the program. It will also allow us to assess the acceptability and adherence to such a format, as well as their links with participants’ use of the support from the hotline [41].

Our study protocol has some limitations. First of all, this study design does not include a control arm that could account for the effects of the passage of time. Although this could provide a more rigorous test of our study hypotheses, a third control arm (e.g., wait-list or treatment as usual) was ruled out due to ethical concerns. Second, though concomitant psychotropic medications as well as the use of adjunctive therapeutic means (e.g., self-help or counseling) will be controlled in our study, subjects will not be instructed to avoid making use of them. While this might be a potential confound in the current study design, the restriction of therapeutic options would also pose an ethical concern, reduce referrals to the study and also be a threat to external validity. Therefore, by monitoring therapeutic (i.e., medication or counseling) use throughout the trial, the current study seeks to balance the internal and external validity and improve the feasibility of the study while efficiently addressing its hypotheses. To summarize, if our study hypotheses are confirmed, our program has the potential to become the first evidence-based option developed for the treatment of stress-related conditions (i.e., the COVID-19 psychological burden) in healthcare workers.

### Study timeframe

Study enrollment will begin in June 2020, by the end of the epidemic peak in the East region of France. The active treatment phase is expected to be finished in September 2020. The completion of follow-up assessments is expected in November 2020 and February 2021. The total sample of 120 participants will be completed by February 2021. The dissemination of first results at international meetings is expected by October 2020. Publication of the findings is planned for March 2021.

## Data Availability

The study protocol has been reported in accordance with the Standard Protocol Items: Recommendations for Clinical Interventional Trials (SPIRIT) guidelines (Additional file 1). The consent form and information material are available from the corresponding author on request.

## Abbreviations

ARQ: Affective Rumination Questionnaire
CBT: Cognitive behavioral therapy
CD-RISC-2: Connor-Davidson Resilience Scale – 2-item version
CEQ: Credibility and Expectancy Questionnaire
CSQ-8: Client Satisfaction Questionnaire – 8-item version
ISI: Insomnia Severity Index
PHQ-2: Patient Health Questionnaire – 2-item version
PSS-10: Perceived Stress Scale – 10-item version
PTSD: Post-traumatic stress disorder
SF-PCL-5: Short Form Posttraumatic Stress Disorder Checklist
VAS: Visual analog scale
